## Discussion

To the best of our knowledge, the e-predictD study will be the first to evaluate the effectiveness and cost-effectiveness of a personalized biopsychosocial intervention based on ICTs, risk prediction algorithms, and DSS for the prevention of depression in primary care. We propose an innovative intervention to prevent depression in primary care. The e-predictD intervention has a broader focus, the biopsychosocial orientation, which goes beyond the exclusively psychological approach. The e-predictD intervention also incorporates elements of “P4 medicine” (precision, predictive, personalized, and participatory medicine) (42), involving GPs and patients and using technological solutions based on ICTs, risk prediction algorithms, DSS, and monitoring and feedback systems. The e-predictD study incorporates approaches based on the UK Medical Research Council for complex interventions, involving different stakeholders in the design and evaluation of the e-predictD intervention, using mixed methods research (qualitative and quantitative), a previous pilot study, and a multicenter cluster randomized trial to evaluate the effectiveness and cost-effectiveness of the e-predictD intervention in preventing depression. The e-predict study also presents several limitations:

(1) The GPs who choose to participate in the e-predictD study may have a different profile (psychosocial orientation, different training or work satisfaction, etc.) to those who do not. Similar biases could occur if a large proportion of patients refuse to participate. It is not easy to obtain information from those GPs and patients who refuse to participate, so it will be difficult to ascertain the direction and magnitude of this possible selection bias. (2) This potential selection bias could also limit external validity (98). In addition, the inferences of this trial will be limited to primary care attenders aged 18–55 years at moderate-to-high risk of depression with internet access and basic technological literacy. Nonetheless, primary care is an ideal setting to carry out primary prevention strategies for depression because many people at risk of depression go to see their GPs. (3) Apart from the only per protocol visit that patients will have with their GPs, the e-predictD is basically an intervention that is unguided and delivered via smartphone; therefore, trial attrition and disengagement are potential issues (99). Reasons for attrition are complex and, in reality, there are contradictory possibilities of drop-out due to dissatisfaction or lack of engagement, as opposed to drop-out due to a sense that the individual feels his/her needs have been met. We will use those evidence-based strategies to maximize engagement and adherence: reducing the length of follow-up questionnaires and giving participants feedback on their progress while filling out the questionnaire, automated tailoring, real-time engagement, gamification and intrinsic motivation to engage, log of past app use, reminders to engage, and a simple intuitive interface and interactions (100). To address the possibility that users may delete the app during the trial, which may hamper follow-up attempts, later follow-ups will occur via the phone numbers provided, rather than via the app. Participants will receive up to three phone calls to complete each assessment and follow-up measures will be accepted as long as they are obtained within 90 days of the planned assessment. In addition, we will use a robust statistical method (multiple imputations) for data missing at random, so we hope that this limitation will be minimized. (4) Although cluster randomization by GP will reduce possible contamination bias, some degree of contamination could occur due to the coexistence in the same PCC of GPs and patients of both control and intervention arms. The magnitude of this bias would be small, but in any case, it would go against the effectiveness hypotheses of the e-predictD study. (5) Since we evaluate a psychosocial intervention in real practice, it is not possible to blind GPs who provide it (55). Both the intervention and active control GP groups could modify their behavior because they feel observed (Hawthorne bias). These behavioral changes in the GPs in the active control group could be influenced by social desirability bias, whereby they could improve the usual care they provide to their patients in the control group; therefore, this last bias would also go against the hypothesis of this study. (6) We use an active control group, whose intervention (brief weekly psychoeducational messages) could have some preventive effect on depression, especially in those patients with a lower risk of depression, which could reduce the differences in the preventive effect between both the e-predictD and the active control groups. (7) The cluster randomization might produce a good balance between the groups at the GP level; however, this does not guarantee a good balance at the patient level (101), which could contribute to confounding bias. We will perform adjusted analyses for variables unbalanced at baseline if necessary. (8) Finally, there could be post-randomization biases (e.g., unbalanced use of antidepressants between the intervention and active control groups during follow-up), which will be addressed by carrying out measurements and adjusted analyses.

If the e-predictD intervention proves to be effective and cost-effective in preventing depression and also has good acceptability and adherence by patients and GPs, its overall impact could be substantial, reducing overall depression burden as well as associated healthcare cost and improving mental health and quality of life. This overall impact would be relevant even if the size of the preventive effect was relatively small since its implementation in primary care and through apps would facilitate its scalability to a large part of the population at risk of depression.

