The GP training consisted of 10 h of face-to-face group workshops during working hours and 5 h of individual online work solving real clinical cases taken from the pilot study. As this study was to be conducted in different Spanish cities, we carried out a training of the trainers to ensure that the GP training was conducted homogeneously and with a minimum quality standard followed in each of the cities. The 10 learning objectives of the GP training were to: (1) understand the e-predictD study in terms of its justification, design, intervention, follow-up, and security protocol; (2) know the risk and protective factors for depression and evidence-based interventions to prevent depression; (3) know how to interpret and communicate to each patient his/her level and profile of risk of depression; (4) undertake active listening about patients' beliefs, expectations, and the impact of information transmitted through e-predict reports and PPPs for depression; (5) know how to detect and empathetically manage patients' negative and positive emotions during the GP–patient interview; (6) know the eight intervention modules included in the e-predictD app; (7) know how to detect and cope with difficulties patients may have in understanding and following the e-predictD intervention; (8) know how to support those patients who are excessively worried by the information given; (9) know how to detect and manage the mental and physical comorbidities most frequently associated with patients at risk of depression; and (10) know how to prepare and conduct the single GP–patient interview of the e-predictD intervention. The methodology of the face-to-face group workshop was very interactive, including role-playing to learn skills, solving clinical cases, and analyzing video recordings of real GP–patient interviews carried out in the pilot study.

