### Safety protocol

In any trial concerned with mental health, there is the potential for psychological distress in participants. Patients in either arm falling into PHQ-9 or/and Generalized Anxiety Disorder (GAD-7) score above 14 and/or reporting suicidal ideation (“nearly every day” in item 9 of the PHQ-9) at baseline and/or during follow-up will be automatically informed regarding their mental health. Through sequential messages over time, they will be suggested to seek further help from their GPs. Additionally, an optional call-back service for individuals requiring further support or direction will be provided. This call-back will occur within 3 days by a staff psychologist who will guide participants into necessary care arrangements.

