#### Outcomes

Our primary outcome is the cumulative incidence of major depression during 12 months of follow-up, assessed through the depression section of the CIDI (68) at 6 and 12 months. As secondary outcomes, we will use measurements of mental and physical quality of life using the SF-12 (69), depressive and anxious symptoms [PHQ-9 (70) and GAD-7 (71)], and the probability of the onset of major depression at 12 months (predictD risk algorithm) (28). All of these will be evaluated at baseline and at 3, 6, 9, and 12 months. We will also make estimates of cost-effectiveness and cost-utility (see economic evaluation below).

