#### Statistical analyses

We will perform all statistical analyses based on the intention-to-treat principle, analyzing all participants according to their randomized treatment and including all of them in the analyses. Although the allocation is by cluster (GPs), inferences will be made exclusively at the patient level. All the analyses will be performed with Stata, version 17 (StataCorp). We will use multiple imputations for dealing with missing data under a missing-at-random framework. The multiple imputations by chained equations procedure will be conducted to obtain at least 20 imputed datasets, and Rubin's rules will be used to combine them (91). To analyze the effect of the intervention on each outcome measure, we will use hierarchical logistic or linear regression models for clustered data. Our primary analysis will be the absolute risk difference in the cumulative incidence of major depression at 12 months of follow-up, adjusted *a priori* for risk of depression at baseline because it is considered strongly predictive of the outcome and thus clinically prognostic (92). Our secondary analyses will include as dependent variables the respective scores for depressive (70) and anxious (71) symptoms, the probability of the onset of major depression in the next 12 months (29), and mental and physical quality of life (69). We will conduct multilevel linear regressions including the GP and time variables as random components, and the variables group, time, the interaction group^*^time, and the respective measurements of the dependent variables at baseline as fixed components. We will calculate standardized mean differences using the margins in Stata. Sensitivity analyses will be conducted: (1) adjusting for those variables unbalanced at baseline between the arms of the trial; (2) performing complete case analysis and adjusting for inverse probability weighting (93) to minimize attrition bias during follow-up. We will evaluate some moderators (age, sex, educational level, anxiety and physical comorbidity, first lifetime depressive episode, and level of risk for depression) and mediators using multilevel structural equation models to describe the causal chain as Kraemer suggests (94). Finally, we will use different definitions of compliance with adherence to the intervention and perform a complier average causal effect analysis (95).

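### Adjusting for antidepressant use during follow-up would add bias of unknown direction to the supplementary analyses; the primary analysis is not affected

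*Protocol article*

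**What the plan says.** The last limitation in the Discussion, item (8), raises possible post-randomisation biases and gives one example with its remedy: "unbalanced use of antidepressants between the intervention and active control groups during follow-up), which will be addressed by carrying out measurements and adjusted analyses". It does not say how use would enter a model, which outcomes are meant, what quantity would be estimated, or whether the result is primary or supplementary. Item (7), just before it, also answers imbalance between arms with adjusted analyses, but for variables measured at baseline.

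The Outcomes section states: "Our primary outcome is the cumulative incidence of major depression during 12 months of follow-up", assessed with the CIDI at 6 and 12 months. Under Statistical analyses, "Our primary analysis will be the absolute risk difference in the cumulative incidence of major depression at 12 months of follow-up", and the only covariate fixed in advance is "risk of depression at baseline because it is considered strongly predictive of the outcome". The same section says "We will perform all statistical analyses based on the intention-to-treat principle". Its one covariate-based sensitivity analysis is "adjusting for those variables unbalanced at baseline between the arms of the trial". No model there includes a covariate for antidepressant use during follow-up.

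**The concern.** Adjustment removes confounding when the covariate precedes treatment. Antidepressant use during follow-up does not, and two routes lead into it.

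- **From the outcome.** A participant who becomes depressed may then be treated. The Safety protocol tells high scorers in either arm that "they will be suggested to seek further help from their GPs". Psychotropic drug use is recorded with the Client Service Receipt Inventory (CSRI) at 6 and 12 months, the same time points as the CIDI, so recorded use can come after the episode.
- **From the arm.** Only intervention GPs are trained. One training objective is to "know how to detect and manage the mental and physical comorbidities most frequently associated with patients at risk of depression". They also review existing treatments, including antidepressants, before an interview that control patients do not have.

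Conditioning on a variable that depends on the outcome shrinks a true effect. If the variable depends on the arm as well, conditioning can also create an effect where none exists. Such an analysis would be presented as removing a bias and read as a check on the primary result, which it could wrongly weaken or strengthen.

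**Working it through.** **1. The plan's own figures.** Inputs from Power and sample size calculation: 20% against 11.2%, two-sided 5%, 80% power, 36 GPs per arm with 10 patients each, intracluster correlation 0.04.

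- Per arm before clustering: n = [1.960 × √(2 × 0.156 × 0.844) + 0.842 × √(0.20 × 0.80 + 0.112 × 0.888)]² / 0.088² = 266.
- Design effect: 1 + (10 − 1) × 0.04 = 1.36, and 266 × 1.36 = 361.8 against 360 stated.

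The figure reproduces and does not depend on the adjustment. It supplies the true difference used below: 11.2 − 20 = -8.8 points.

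**2. Assumptions.** The article gives no antidepressant rates. Write a1 for the proportion of cases who use an antidepressant, a0 for the proportion of non-cases, and p for the incidence in an arm.

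**3. Formula.** In each arm:

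- use: q = p·a1 + (1 − p)·a0
- risk among users: p·a1 / q
- risk among non-users: p·(1 − a1) / (1 − q)

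A linear model of outcome on arm and use averages the two within-stratum differences with weights qC·qI/(qC + qI) for users and (1 − qC)(1 − qI)/(2 − qC − qI) for non-users, where C is control and I is intervention.

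**4. Worked case: a1 = 50%, a0 = 8% in both arms.**

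- qC = 0.20 × 0.50 + 0.80 × 0.08 = 0.164; qI = 0.112 × 0.50 + 0.888 × 0.08 = 0.127.
- Users: 0.056/0.127 − 0.100/0.164 = 0.441 − 0.610 = -0.169.
- Non-users: 0.056/0.873 − 0.100/0.836 = 0.064 − 0.120 = -0.055.
- Weights: 0.0716 and 0.4270.
- Adjusted difference: (0.0716 × -0.169 + 0.4270 × -0.055) / 0.4986 = -0.072.

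A logistic model with standardised risks also gives -7.2, from risks of 11.9% and 19.1% (risk ratio 0.62 instead of 0.56).

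**5. Range, in percentage points (use shown as cases/non-cases).**

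| True difference | Use, control | Use, intervention | Adjusted |
|---|---|---|---|
| -8.8 | 30/10 | 30/10 | -8.4 |
| -8.8 | 50/8 | 50/8 | -7.2 |
| -8.8 | 60/8 | 60/8 | -6.5 |
| -8.8 | 50/10 | 40/5 | -4.9 |
| -8.8 | 50/10 | 60/20 | -10.8 |
| 0 | 50/8 | 50/8 | 0 |
| 0 | 50/8 | 50/12 | -1.4 |
| 0 | 50/8 | 50/16 | -2.5 |
| 0 | 50/8 | 50/20 | -3.4 |
| 0 | 50/8 | 40/5 | +2.2 |

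**6. Effect on the test.** In simulated trials of the planned size (36 GPs × 10 per arm, intracluster correlation 0.04, cluster-robust test, 4,000 runs), the analysis without the covariate keeps power near 80% and type I error near 5%. With the covariate and a true zero, type I error is about 22% when use goes from 50/10 in control to 60/20 in intervention, and about 15% when it goes from 50/10 to 40/5. With a true -8.8 and use lowered from 50/10 to 40/5, power falls to about 40%.

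**The case against.** - **The promise is brief and outside the analysis section.** It is part of one sentence under limitations, offered as an example of what could occur. A reader might infer that the primary estimate will be biased. The documents do not support that: the primary model is fixed with baseline risk as its only covariate, and the listed covariate sensitivity analysis and the economic models also use baseline variables. This stands and limits the severity.
- **No model form is stated.** The plan already includes mediation models and a complier analysis, and the full analysis plan may specify a suitable causal method. That is possible. Still, the sentence follows item (7) in treating imbalance as something adjustment cures, and it names neither a target quantity nor a time order.
- **Intention to treat.** A reader might infer an outright contradiction. The article defines the principle as analysing everyone by randomised arm and including all of them. A supplementary model with an extra covariate can do both. What it changes is the quantity estimated.
- **The routes into drug use are not documented.** The safety messages go to both arms and do not mention antidepressants. The training objective concerns comorbidity, not prescribing. Some use will also precede onset or serve another indication. An effect of arm on use is therefore plausible rather than shown.
- **The bias may be small.** At 20% of cases against 10% of non-cases, equal across arms, the adjusted difference is -8.7. This also stands: size and direction are unknown.

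**Conclusion.** Item (8) is wrong as written, with moderate severity. It proposes ordinary adjustment as the cure for an imbalance in a variable that can follow the outcome and may be changed by the intervention. Under the assumed rates, equal use across arms shrinks a true -8.8 points to between -8.4 and -6.5. If arm also affects use, the estimate can move to about -5 or -11. A true zero is preserved when use follows the outcome equally in both arms. Otherwise it becomes about -1.4 to -3.4 when the intervention raises use among non-cases from 8% to 12–20%, or about +2.2 when it lowers use from 50/8 to 40/5. The adjusted result therefore cannot be assumed conservative or anti-conservative. All of these figures rest on assumed usage rates.

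The harm is confined to the supplementary analyses promised in item (8). It would reach the trial's conclusions only if those results were used to reinterpret or replace the primary one.

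**What to change.** Replace the remedy in item (8) with text to this effect:

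- Covariate adjustment is limited to variables measured at baseline.
- The primary and secondary estimates count outcomes regardless of antidepressant use during follow-up.
- Antidepressant use during follow-up is reported by arm, descriptively.
- If its role is of interest, it is studied only as a separately defined exploratory analysis that uses the order in time of drug use and onset, for example within the mediation analysis already planned, and that cannot replace or correct the primary result.

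The cost is a short wording change in the protocol, carried into the analysis plan. No new data are needed for the first three points, because the CSRI already records psychotropic drugs. The primary analysis and the sample size stay as they are.

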## Ethics statement

This protocol involving human participants was reviewed and approved by the Ethics Committee in each participating Spanish city: Regional Research Ethics Committee of Malaga, IDIAP Jordi Gol Clinical Research Ethics Committee (Barcelona), Clinical Research Ethics Committee of Aragon (CEICA), Clinical Research Ethics Committee of the Health Area of Salamanca. The participants provided written informed consent to participate in this study.

## Data management

The management of the study data will be carried out in accordance with Regulation (EU) 2016/679 of the European Parliament and of the Council of April 27 2016 on the protection of natural persons with regard to the processing of personal data and the free circulation of these data; and also in accordance with Spanish laws: Organic Law 3/2018, of December 5, on the Protection of Personal Data and guarantee of digital rights, as well as Law 41/2002, of November 14, basic regulating autonomy of the patient and of rights and obligations regarding information and clinical documentation, among others. All study participants will be informed about the purpose of the study and the use and reuse of the data. They will sign an informed consent to join the study, which, together with the study protocol, has been validated by the competent ethics committees. After recruitment, the personal data of the participants will be removed from all data and stored in a password-protected encrypted database. Each participant will receive a code that will only be linked to the data, except in case of medical emergency. To ensure data quality, the research coordinator or person designated by him/her will implement and maintain quality assurance and control procedures with written standard operating procedures to ensure that the study is conducted and that the data is generated, documented, and reported in accordance with the protocol. Quality control procedures will be implemented starting with the data entry system, and data quality control checks will be performed on the database. The data, which will be collected in the framework of this project, will be used to study depression prevention. Access to the data will be through an administrator user in a back office or through export to CSV format. The data will belong to the research group according to the privacy policy and will be located in a database within servers, which will be blocked with encrypted files and passwords. The project research team will be responsible for the curation-purification and conservation of the data. For the preservation of the data, periodic backup copies will be made.

## Data sharing

The data generated during this study will include detailed information on the protocols and analyses used, to allow their reproducibility and future analyses by other groups. We recognize and support the principles of data sharing. The data generated from this research will be made available to affiliated investigators through secure and anonymized databases. Only investigators with specific independent ethics committee approval will have access to any anonymized data. The research coordinator of the e-predictD study can be contacted for de-identified data requests. Consent for such data sharing will be integral to enrollment in the study, and our participants will be asked about their willingness to have their data shared to advance health research.
